#### Sever COVID-19

Severe COVID-19 disease is defined as COVID-19 disease resulting in blood oxygen saturation < 90%, signs of pneumonia and signs of severe respiratory distress. Occurrence of COVID-19 disease will be solicited throughout follow-up to collect information on laboratory-confirmed diagnosis or not [12]. In the present study, the occurrence of COVID-19 is based on clinical manifestations diagnosed by health professionals or/and the polymerase chain reaction (PCR) test.

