#### Specific objectives

To Estimate the incidence of different types of serious adverse events (SAEs) within 13 weeks in all enrolled vaccinated individuals after either the first or second booster vaccination with AstraZeneca.To estimate the incidence of different types of adverse events of special Interests (AESIs) within 13 weeks.To estimate the incidence of COVID-19 after either the first or second booster dose of A in all enrolled people.

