### Study outcomes

#### Serious adverse events (SAEs): hospitalization, death

Serious adverse events (SAEs) is defined as any over-night hospitalization or death. SAEs that lead to in-patient hospitalizations will be reported by the participant or their next of kin, and SAEs that results in death will be reported by their next of kin [12].

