### Source documents

The data sources for the exposure of interest will be participants and registered data. We should note that by adding the National code for each participant, all required information regarding the previous history of vaccination will be added to the web based questionnaire. The data source for covariates will be the participants as well. The data sources for the study outcomes will be the questionnaires completed by the participants (or their next of kin) as well as documentation from hospital and the universities committees as well as the national committee.

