### Statistical analysis

In the present study, the data on SAEs and AESIs will be included for the whole cohort population. People who do not report any event(s) will be considered as participants without event(s). As AESIs can occur even after 42 days following the first booster dose, the sensitivity analysis will be done excluding those AESIs occurring within the first 12 days after the second booster dose.

We will calculate the frequency and proportion of participants reporting AESIs and SAEs by time since vaccination. For the proportions, 95% confidence intervals will be calculated using an exact method.Observed-to-expected analyses will be conducted for SAEs and AESIs with an unknown risk window (most likely situation). The observed incidences for AESIs will be compared with background rates from the most appropriate sources. The expected rate will be age-stratified, and the standardized incidence ratio (SIR) will be calculated.Incidence rate of severe COVID-19 disease (any COVID-19 disease diagnosed by a healthcare professional, laboratory-confirmed COVID-19, hospitalization for COVID-19, COVID-19 requiring intensive care unit (ICU) admission, COVID-19 disease resulting in death) will be calculated after either the first or the second booster dose of the AstraZeneca and within the period of follow-up.

The present study will be performed in line with the international ethical guidelines for epidemiology studies published by the Council for International Organizations of Medical Sciences (CIOMS), the Declaration of Helsinki and its amendments, good epidemiological practice (GEP) guidelines and the Iran National Committee for Ethics in Biomedical Research. Data protection and privacy regulations will be strictly observed in capturing, forwarding, processing, and storing individuals’ data. The study protocol and informed consent forms will be reviewed and approved by the Iran National Committee for Ethics in Biomedical Research.

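### Severe COVID-19 is defined in two incompatible ways: the outcomes section joins three signs with 'and', while the analysis section counts everything from any diagnosed case to death

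*Protocol article*

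**What the plan says.** The Study outcomes section, under *Sever COVID-19*, gives the definition: "Severe COVID-19 disease is defined as COVID-19 disease resulting in blood oxygen saturation < 90%, signs of pneumonia and signs of severe respiratory distress". It has no 'or' or 'any of', and it mentions neither ICU admission nor death. The same paragraph then turns to COVID-19 of any severity: "the occurrence of COVID-19 is based on clinical manifestations diagnosed by health professionals or/and the polymerase chain reaction (PCR) test".

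The Statistical analysis section describes the numerator differently. It begins "Incidence rate of severe COVID-19 disease (any COVID-19 disease diagnosed by a healthcare professional, laboratory-confirmed COVID-19, hospitalization for COVID-19" and continues "COVID-19 requiring intensive care unit (ICU) admission, COVID-19 disease resulting in death) will be calculated after either the first or the second booster dose". The three signs do not appear there.

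Three other places bear on the point:

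- The third specific objective concerns COVID-19 as a whole: "To estimate the incidence of COVID-19 after either the first or second booster dose of A in all enrolled people". The end of the Discussion, however, names severe COVID-19 as one of the three outcomes under investigation.
- Table 2 lists, in its follow-up column, a COVID-19 test, symptom onset date, hospitalization with its reason, ICU admission, death and reason of death. It lists no oxygen saturation, no pneumonia item and no respiratory-distress item. The nearest entry is acute respiratory distress syndrome in the AESI column, which is a diagnosis and not a recorded sign.
- Source documents says "The data sources for the study outcomes will be the questionnaires completed by the participants (or their next of kin", and the sentence goes on to add hospital, university-committee and national-committee documentation.

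**The concern.** An outcome needs one rule that two analysts would apply alike. Here the sentence that defines severe COVID-19 and the sentence that says what will be counted under that name select different people.

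Read alone, the definition can class a fatal or ICU case as not severe, although the analysis section places both under severe disease. Read alone, the analysis wording can class a mild, laboratory-confirmed infection as severe.

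What is at stake is the interpretability of the severe COVID-19 rate after the booster. Depending on which sentence the analyst follows, the reported figure could describe a small, heavily documented subgroup or all diagnosed COVID-19, and a reader of the report could not tell which.

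**Working it through.** **No figure to reproduce.** The protocol gives no expected rate of severe COVID-19 and no frequency for any of the three signs. Its one design figure, 10,000 per vaccine for an event of 1 per 3,333 (3 × 3,333 = 9,999), does not depend on this outcome.

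**Step 1: score the same records under each rule.** The records are hypothetical and only show where the two texts part.

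| COVID-19 case | Outcome definition (all three signs) | Analysis wording |
|---|---|---|
| Death at home, no oximetry | not severe | counted |
| ICU admission, one sign absent or unrecorded | not severe | counted |
| Inpatient, saturation 86%, pneumonia, no severe distress recorded | not severe | counted |
| ICU admission or death, all three signs present | severe | counted |
| Mild PCR-confirmed case at home | not severe | counted |

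The rules agree on only one of the five rows. Every diagnosed case that meets the three-sign rule is also counted under the analysis wording, so the first set lies inside the second and the second rate cannot be the lower one.

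**Step 2: direction.** Take as reference a category that includes COVID-19 ICU admissions and deaths but not mild diagnosed cases. The outcome definition misses the first two rows, and the analysis wording adds the last. The errors run in opposite directions, so the net bias depends on which sentence is followed. The protocol does not say.

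**Step 3: does 'all of' versus 'any of' matter?** This is an illustration on assumed values only. Suppose each sign is present independently with probability q among clinically severe cases. 'All of' captures q³ and 'any of' captures 1 − (1 − q)³.

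- q = 0.6: 0.6³ = 22%; 1 − 0.4³ = 94%
- q = 0.8: 0.8³ = 51%; 1 − 0.2³ = 99%
- q = 0.9: 0.9³ = 73%; 1 − 0.1³ = 99.9%

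Neither q nor independence comes from the protocol. The lines show only that the conjunction is not a cosmetic detail. They do not estimate a bias in this study.

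**Step 4: can the definition be scored from the listed data?** Hospitalization, ICU admission and death can be scored from Table 2, with reasons recorded for hospitalization and death. The three signs cannot. They would have to come from hospital or committee files, which may not exist for someone who died at home.

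**The case against.** The tempting stronger reading is that the study omits COVID-19 deaths and ICU stays and so undercounts severe disease. The document does not support that, for four reasons.

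- The analysis section names ICU admission and death explicitly. Because it also takes in every diagnosed or laboratory-confirmed case, following it as written would overcount.
- Deaths and ICU cases that show all three signs do meet the outcome definition.
- These patients are not lost to the safety evaluation: "Serious adverse events (SAEs) is defined as any over-night hospitalization or death". Any COVID-19 death or overnight stay is therefore counted as an SAE.
- The signs need not rest on lay reports. Source documents adds hospital and committee documentation, the recruitment and follow-up section sends all SAEs to committee review, and the quality assurance section provides for examination of medical records. Nor does the protocol say that an unrecorded sign counts as absent. It says only that people who report no event are treated as event-free.

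Two readings of the wording could also be offered in defence. The comma list in the definition may be a loose 'any of', and the source cited there is not available to settle it. The parenthesis in the analysis section may be meant as a list of separate rates.

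The four reasons stand, and they remove any claim of a known undercount. The two readings do not rescue the text. A loose 'any of' still leaves two analysts with different counts and still omits ICU admission and death. If the parenthesis lists separate rates, the label 'severe' is wrong for its first two entries, and the defined outcome is not among them.

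**Conclusion.** The point holds as an inconsistency between two definitions of one named outcome. The definition in Study outcomes, read literally, is too narrow: it excludes COVID-19 deaths, ICU admissions and hypoxic cases in which all three signs are not present or recorded. The wording in Statistical analysis is too broad, because it includes every diagnosed case.

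The net direction of bias is not settled, and its size cannot be computed from the document. The conclusion rests on a literal reading of 'and', and on Table 2 being a fair account of the main follow-up variables. The effect is confined to the severe COVID-19 rate. SAE counts and the sample size are untouched, and the specific objective on overall COVID-19 incidence does not depend on the three-sign rule.

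**What to change.** Write one definition of severe COVID-19 and use it in both Study outcomes and Statistical analysis:

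1. State whether the three signs are 'any of' or 'all of'. That choice is for the investigators.
2. Let ICU admission for COVID-19 and death due to COVID-19 qualify without requiring all three signs. Both are already collected and already listed under severe disease in the analysis section.
3. Report any diagnosed COVID-19, laboratory-confirmed COVID-19 and hospitalization for COVID-19 as separate rates outside the severe numerator. The first of these also serves the stated objective on overall incidence.
4. State the source from which the signs will be taken, since Table 2 lists no item for them.

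The cost is a few sentences in two sections. ICU admission and death need no new data. The signs need either the hospital and committee documentation already named as a source or an added item. The downside is that the severe category may include somewhat milder cases than the all-three rule would.

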### Data management

We will develop a data management plan (DMP) before data collection begins and will describe all functions, processes, and specifications for data collection and cleaning. Study staff will enter data in an electronic questionnaire at several time points. The study staff will enter the participants’ information, contact details and data on the exposure at the time of vaccination and all other covariates.

### Data security

In the present study, we stored the key-coded data in a secured database located in Iran. Data will be handled in line with all applicable data protection and privacy laws. No unauthorized persons will have access to the data. Data will be archived for 10 years, as per national regulations, and will then be destroyed. Data will be stored in a secure server environment and will be provided to researchers with an approved proposal by the project data manager. Analyses will be done on de-identified data by authorized researchers.

### Source documents

The data sources for the exposure of interest will be participants and registered data. We should note that by adding the National code for each participant, all required information regarding the previous history of vaccination will be added to the web based questionnaire. The data source for covariates will be the participants as well. The data sources for the study outcomes will be the questionnaires completed by the participants (or their next of kin) as well as documentation from hospital and the universities committees as well as the national committee.

### Data retention and archiving

Documents that individually and collectively permit evaluation of the study conduct and the quality of the data produced will be retained for 10 years in accordance with good pharmacoepidemiological practice guidelines. This will include the analytical data, analysis programs, and all output generated.

### Quality assurance, monitoring, and reporting

For each province, a Co-PI will be selected who has direct communication with the PI and the central team. Remote and on-site monitoring of the study conduct will be performed throughout the study period to assess the accuracy and completeness of the data. The study site may be subject to a quality assurance visit. If so, the site will be contacted in advance to organize a monitoring visit. The investigator and site staff will assure direct access to all study documents for quality assurance monitors. The central team, included the authors of the present study, will control the quality of data once a week to identify errors, outliers and missing data. Furthermore, we will extract 1% of data randomly and contact participants to make sure they are adequately informed about the present study and know how to complete web based follow-up questionnaires. The examination of medical records will be conducted in the KUMS and the national committees. The committees will investigate medical records to approve or reject the association of the booster dose with a health outcome.

### Interim analyses and reporting

For the study outcomes, interim analyses will be performed monthly but the formal report will be released within 1.5, 3, and 6 months. Such reports will be disseminated to all formal organizations and Iranian medical universities (including the Iranian Ministry of Health and Medical Education and WHO by request). In addition, the report will be published in relevant medical journals.

### Final analyses and reporting

Final analyses will be conducted and a full study report will be written within 4 weeks after database lock. Study results will be shared with the national regulatory authorities for regulatory review, and with the national immunization program to inform public health policy decisions.

### Study management

This study will be conducted by the principal investigator, Co-PIs. In addition, scientific advisors contribute to the development of materials, recruitment, training and management of sites, the electronic data capture, and data management and analyses. The Investigator and all study staff will conduct the present study in line with the ethics protocols of the Iran National Committee for Ethics in Biomedical Research. All human resources involved in the conduct of this study will be qualified by education, training, and experience to accomplish their tasks. For the purpose of this study, as well as in person communication with the PI and the central team, the co-PI and all other recruitment staff will take part in two separate training sessions held by the central team and a team from Iranian CDC.

### Statistical analysis

In the present study, the data on SAEs and AESIs will be included for the whole cohort population. People who do not report any event(s) will be considered as participants without event(s). As AESIs can occur even after 42 days following the first booster dose, the sensitivity analysis will be done excluding those AESIs occurring within the first 12 days after the second booster dose.

We will calculate the frequency and proportion of participants reporting AESIs and SAEs by time since vaccination. For the proportions, 95% confidence intervals will be calculated using an exact method.Observed-to-expected analyses will be conducted for SAEs and AESIs with an unknown risk window (most likely situation). The observed incidences for AESIs will be compared with background rates from the most appropriate sources. The expected rate will be age-stratified, and the standardized incidence ratio (SIR) will be calculated.Incidence rate of severe COVID-19 disease (any COVID-19 disease diagnosed by a healthcare professional, laboratory-confirmed COVID-19, hospitalization for COVID-19, COVID-19 requiring intensive care unit (ICU) admission, COVID-19 disease resulting in death) will be calculated after either the first or the second booster dose of the AstraZeneca and within the period of follow-up.

The present study will be performed in line with the international ethical guidelines for epidemiology studies published by the Council for International Organizations of Medical Sciences (CIOMS), the Declaration of Helsinki and its amendments, good epidemiological practice (GEP) guidelines and the Iran National Committee for Ethics in Biomedical Research. Data protection and privacy regulations will be strictly observed in capturing, forwarding, processing, and storing individuals’ data. The study protocol and informed consent forms will be reviewed and approved by the Iran National Committee for Ethics in Biomedical Research.

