**Methods:**

The present study is an active COVID-19 vaccine safety surveillance through an observational prospective cohort study that will be conducted in vaccination centers in Iran. The study will be conducted in twelve provinces of Iran. Study sites are vaccination centers where the AstraZeneca vaccine is administered to the cohort population. The study population includes all individuals who have received two doses of Sinopharm or Sputnik V vaccines and either the first or second booster dose of AstraZeneca according to the national guidelines for immunization in Iran in 2023. We are planning to include 30,000 eligible people in this study. Each individual will be followed up for 13 weeks after either the first or second booster dose of the AstraZeneca vaccine. Furthermore, convenience sampling is used to include participants in the present study. Participation in the study will be strictly voluntary.

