### Sample size estimation

Regarding the WHO’s protocol, the sample size required to rule out an event with a frequency of 1 per 3,333 with a 95% confidence interval is 10,000 per vaccine [11]. Therefore, we are planning to include 20,000 and 10,000 eligible people with previous vaccination with Sinopharm and Sputnik V respectively. Regarding the higher proportion of immunization coverage for the Sinopharm vaccine compared to Sputnik V in Iran, we will include more vaccinated people with the Sinopharm vaccine in the present study. Participants will be considered to have completed the study when they have completed the last questionnaire 13 weeks after the booster dose. The end of the study is defined as the point at which the last subject enrolled has reached the 3 months follow-up period. In this study, convenience sampling will be used to include eligible participants until achieving the required sample size.

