## Discussion

As part of the effort to monitor COVID-19 vaccine safety in Iran, this study aims to evaluate the safety of heterologusbooster vaccination with AstraZeneca in people vaccinated with Sinopharm or Sputnik V vaccines in Iran. The magnitude of the increased risk of serious adverse events after heterologous booster vaccination, if there is any, is still not well understood. Moreover, there are few large cohort studies that identify SAEs among people with heterologous booster vaccination especially among those with vector based or inactivated primary vaccination [13–15]. Accordingly, we decided to set up active COVID-19 vaccine safety surveillance through an observational prospective cohort study in Iran.

To the best of our knowledge, in Iran, there is just an ongoing cohort study by Aliyari et al. for safety signal detection after primary vaccination with COVID-19 vaccines which in turn provides an opportunity to raise awareness of pharmacovigilance among policymakers and healthcare providers, and encourage a perception that pharmacovigilance falls within the scope of a vaccine safety surveillance system [16].

Globally, there are various ongoing studies to investigate the risks of COVID-19 vaccines. For example, Kant et al. (2022), in Netherland, examined differences in the frequencies of ‘well-known’, systemic adverse events following immunization (AEFIs) for four COVID-19 vaccines (AstraZeneca’s Vaxzevria®, Moderna’s Spikevax®, Pfizer’s Comirnaty®, and the Janssen vaccine) in which the frequency of serious AEFIs was the highest for the AstraZeneca (0.228%) and persons receiving the first dose of the AstraZeneca and Janssen vaccines and the second dose of the Moderna vaccine experienced AEFIs mostly [17]. In a study by Consantiono et al.(2022), in Italy, AstraZeneca and Pfizer- BioNTech vaccines indicated a good safety profile but people who received AstraZeneca had a higher number of AEFI than the group who received Pfizer- BioNTech (83% vs. 42%) [18]. In another study (2022) findings supported the safety of the Oxford/AstraZeneca COVID-19 vaccine among healthcare workers in Saudi Arabia so that all the side effects were mild-to-moderate [19]. Also, there are other studies in Africa [20], the USA [6, 21, 22], Canada [23], China, Hong Kong [24, 25], Czech Republic [26], Netherland [27], Italy [28], Korea[29], Spain [30], etc. to explore and measure the causal association between vaccines and adverse events.

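### The sample size is justified separately for Sinopharm and Sputnik V recipients, but no objective or stated estimate is by primary series

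*Protocol article*

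**What the plan says.** Under Sample size estimation, the protocol article takes from a WHO protocol that "the sample size required to rule out an event with a frequency of 1 per 3,333 with a 95% confidence interval is 10,000 per vaccine", and concludes that "we are planning to include 20,000 and 10,000 eligible people with previous vaccination with Sinopharm and Sputnik V respectively". The total of 30,000 is the sum of two group targets, and the precision claim is applied to each group.

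The first of the Specific objectives estimates SAE incidence "within 13 weeks in all enrolled vaccinated individuals after either the first or second booster vaccination with AstraZeneca". The COVID-19 objective is likewise for all those enrolled. The objective on adverse events of special interest (AESIs) names no population.

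The Statistical analysis section opens by saying that "the data on SAEs and AESIs will be included for the whole cohort population". It continues: "We will calculate the frequency and proportion of participants reporting AESIs and SAEs by time since vaccination". Exact 95% confidence intervals follow. The expected rates for the SIR are stratified by age. The COVID-19 rate is described for the first or the second booster. Primary series does not appear in this section. Booster number is treated separately only in a sensitivity rule on AESI timing.

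**The concern.** A per-group sample size justification is a promise of per-group precision. Here it is made for Sinopharm and for Sputnik V recipients, and then no estimate is named to which it applies. Read together, the objectives and the analysis section lead to one figure per outcome for the whole cohort.

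That figure is a weighted average whose weights come from the recruitment targets (two thirds Sinopharm, one third Sputnik V) and from convenience sampling. If risk after the AstraZeneca booster differs by primary series, the average moves towards the larger group. A raised risk confined to the smaller Sputnik V group is then shrunk and harder to detect, although the analysis uses three times as many people. The results are meant for the regulator and the immunization program, who would want to know which primary series an incidence applies to.

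**Working it through.** **Inputs from the protocol article.** Event frequency p = 1/3,333, confidence 95%, 10,000 per vaccine, 20,000 Sinopharm and 10,000 Sputnik V (Sample size estimation); exact 95% intervals and an SIR against background rates (Statistical analysis).

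**Assumptions, not in the article.** Equal background risk in the two groups, the 2:1 mix achieved as planned, and 13-week background risks b of 1 in 10,000, 1 in 3,333 and 1 in 1,000.

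**1. The article's own figure.** The smallest n for which zero events excludes p at one-sided 95% is ln(0.05)/ln(1 − 1/3,333) = 9,983; the rule of three gives 3 × 3,333 = 9,999. With n = 10,000 the chance of at least one event is 1 − (1 − 1/3,333)^10,000 = 0.950. The stated 10,000 is reproduced. (With 0.025 in the tail, n would be 12,293, so the stated figure is the one-sided bound.)

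**2. What zero events would exclude.** The upper bound is 1 − 0.05^(1/N):
- Sputnik V, N = 10,000: about 1 in 3,339
- Sinopharm, N = 20,000: about 1 in 6,677
- Pooled, N = 30,000: about 1 in 10,015, which bounds only the 2:1 average risk

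**3. Dilution of the SIR.** Pooled SIR = (20,000·b·SIR_Sinopharm + 10,000·b·SIR_Sputnik)/(30,000·b) = (2·SIR_Sinopharm + SIR_Sputnik)/3.

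| SIR in one series, 1 in the other | Pooled, Sputnik V only | Pooled, Sinopharm only |
|---|---|---|
| 2 | (2 + 2)/3 = 1.33 | (4 + 1)/3 = 1.67 |
| 3 | (2 + 3)/3 = 1.67 | (6 + 1)/3 = 2.33 |
| 5 | (2 + 5)/3 = 2.33 | (10 + 1)/3 = 3.67 |

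The excess shrinks by two thirds for a Sputnik V signal and by one third for a Sinopharm signal.

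**4. A small example.** Three events among 10,000 Sputnik V recipients and none among 20,000 Sinopharm recipients give 3.0 per 10,000 (exact 95% CI 0.62 to 8.76) in the Sputnik V group, but 1.0 per 10,000 (0.21 to 2.92) pooled. The pooled upper limit lies below the Sputnik V point estimate.

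**5. Power of the observed-to-expected comparison.** Exact Poisson test, one-sided 0.025, true SIR of 3 in one series and 1 in the other. For Sputnik V the mean count is 10,000·b·3 in its own group and 20,000·b + 10,000·b·3 pooled. At b = 1/10,000, the group expects 1 event, rejects at 4 or more and has mean 3; the pooled cohort expects 3, rejects at 8 or more and has mean 2 + 3 = 5.

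| Background | Sputnik V only: own group | Sputnik V only: pooled | Sinopharm only: own group | Sinopharm only: pooled |
|---|---|---|---|---|
| 1 in 10,000 | 0.353 | 0.133 | 0.554 | 0.401 |
| 1 in 3,333 | 0.676 | 0.432 | 0.945 | 0.889 |
| 1 in 1,000 | 0.993 | 0.888 | about 1 | about 1 |

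Separate analyses mean two tests where pooling has one. Halving the level to 0.0125 for the Sputnik V test gives power 0.185 (reject at 5 or more), 0.676 (still 8 or more) and 0.987 (19 or more), each still above the pooled value.

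**6. Booster number.** The article sets no numbers by booster. If 50%, 25% or 10% of the 10,000 Sputnik V recipients had their second booster (an assumption), that cell would have 5,000, 2,500 or 1,000 people and zero events would exclude only about 1 in 1,670, 1 in 835 or 1 in 334.

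**The case against.** The strongest reply is that pooling is inferred, not declared. The opening sentence of the analysis section may be only an analysis-set rule, since the next sentence deals with people who report no event. The wording on first or second booster also defines enrolment and exposure elsewhere in the article, and can be read one booster at a time. This is a condensed article, and table breakdowns are often left to an analysis plan. All of that stands against a stronger reading, that the article rules out results by series; it does not. The point survives because it does not rest on that sentence alone: the SAE and COVID-19 objectives are positively stated for everyone enrolled, while the sizing in the same document is by series.

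Three further inferences are tempting and unsupported:
- **A planned contrast of vaccine platforms.** The Discussion says that large cohorts are few, "especially among those with vector based or inactivated primary vaccination". That is an evidence gap covering both series; no comparison is announced.
- **A main analysis by booster number.** No size is set for those cells, so the acceptance of wider intervals does not extend to them.
- **Events would go unseen.** SAEs and AESIs are reviewed case by case by university and national committees, with vaccination history linked. With no background, pooling does not lower the chance of seeing at least one event. It lowers the estimated rate and weakens the SIR when there is background.

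It is also fair that an average over all AstraZeneca booster recipients is a legitimate quantity. It is simply not the one whose precision was justified.

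**Conclusion.** The point holds as a mismatch inside the article: size is justified for each primary series, objectives and stated estimates are for the whole cohort, and no estimate is named by series. It is a matter of stating which estimates are the main ones, and does not put the sample size in doubt. Under equal background risks and a 2:1 mix, a signal confined to Sputnik V recipients loses two thirds of its excess in the pooled SIR, and power falls at each of the three backgrounds tried; the loss is milder for a Sinopharm-only signal and disappears when events are common. The SIRs and background risks are illustrative, as the article gives none. If the two series carry the same risk, pooling biases nothing and is more precise, but the study cannot assume that in advance. For booster number no dilution can be calculated, because the mix is not given.

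**What to change.** In the Specific objectives and the Statistical analysis section, state that the main proportions with exact confidence intervals, the incidence rates and the SIRs will be given separately for Sinopharm and Sputnik V recipients. Give the whole-cohort figure as secondary, with the mix it reflects. Within each series, report first and second booster descriptively, with the achieved number in each cell and the event frequency that number can exclude.

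No new data are needed: vaccination history is linked for each participant, and vaccine brand and dose are recorded. The cost is wording, more tables and wider intervals per series than pooled, which the per-series sizing has already accepted.
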